### Statistical considerations

The number of participants needed in the trial was originally based on estimated event rates, using the Aspirin in Reducing Events in the Elderly (ASPREE) trial populationDFS^51^ which has similar demographic characteristics to the STAREE population, and on the magnitude of the treatment effect anticipated as a result of the LDL-C lowering effect of atorvastatin.

### Modifications triggered by COVID-19

The recruitment rate in Australia was impacted by the COVID-19 pandemic. In addition, STAREE was originally planned as an international endeavour with proposed funding and recruitment across multiple regions including Australia, however in late 2020 it became evident that the proposed funding for recruitment outside of Australia would not be secured. These developments were considered in July 2021 in finalisation of the trial design, reduction in the sample size from an original target of n=18 000 and corresponding power calculation to allow for feasible completion of the trial in Australia alone.

### Sample size

The sample size requirements are summarised in table 1 for detecting relative risk as HRs with a two-sided significance level of 5% and adopting a closed testing procedure of the two co-primary endpoints. The key assumptions of the power calculation are:

Loss to follow-up will occur at a rate of 2% of study participants per annum (loss to follow-up includes those due to death and is expected to be minimised through good retention of participants and the ability to access medical records or perform record linkage for participants who cease in-person assessment). Hence an average of 6.0 years of follow-up time per participant is expected by the anticipated end of the trial in December 2025, at which time the required number of co-primary endpoints are expected to have accrued.An age structure of STAREE participants of 56%: 27%: 12%: 5% in the respective age bands 70–74 years: 75–79 years: 80–84 years: 85+ years. These proportions are based on recruitment of the initial approximately 7500 participants to late 2020.With treatment adherence statins will reduce the rate of major cardiovascular events by 25% and the rate of disability-free survival by 18%.Treatment crossover will occur and impact the HR that will be observed in intention-to-treat analyses. In the first year of follow-up, we assume 8% of participants randomised to statin will cease taking their study medication. Thereafter we assume 3% of participants per annum in the statin group will cease taking study medication. In the first year of follow-up, we assume 1% of participants in the placebo group will commence open-label statin. Thereafter, we assume 3% of participants per annum in the placebo group will commence statin therapy. Further, we assume that there will be no subsequent treatment ‘re-crossovers’. It is assumed that the effects of statin use and non-use outside use of study medication is the same as the effects of randomised statin and placebo, respectively.Rates of the co-primary endpoint death, dementia or persistent physical disability in the placebo group of 18.3 per 1000 person-years (70–74 years), 33.9 per 1000 person-years (75–79 years), 65.7 per 1000 person-years (80–84 years) and 115.4 per 1000 person-years (85+ years) (see online supplemental appendix 4). To allow for a healthy participant effect at recruitment, it is assumed that these event rates will be observed from the start of the third year of an individuals’ follow-up and that in the first and second year of follow-up the corresponding rates, respectively, will be zero and half of that of the third year of follow-up.Major cardiovascular event rates in the placebo group, according to age at randomisation, of 9.5 per 1000 person-years (70–74 years), 11.5 per 1000 person-years (75–79 years), 18.5 per 1000 person-years (80–84 years) and 24.5 per 1000 person-years (85+ years).

10.1136/bmjopen-2022-069915.supp5Supplementary data

**Table 1 T1:** Sample size requirement and power justification for the STAREE (STAtins in Reducing Events in the Elderly) trial’s co-primary endpoints

Co-primary endpoint	Effect size (relative reduction in risk for statin group vs placebo in intention-to-treat analysis based on treatment adherence assumptions)	Power	Required number of events	Required number of participants based on assumed event rates and follow-up
Major cardiovascular events (first occurrence of cardiovascular death, non-fatal myocardial infarction or non-fatal stroke)	20.2%	80.0%	619	9631
Disability-free survival (first occurrence of dementia, persistent physical disability or death)	14.5%	83.1%	1397	9631

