**Methods and analysis:**

We will conduct a double-blind, randomised placebo-controlled trial among people aged 70 years and over, recruited through Australian general practice and with no history of clinical CVD, diabetes or dementia. Participants will be randomly assigned to oral atorvastatin (40 mg daily) or matching placebo (1:1 ratio). The co-primary endpoints are disability-free survival defined as survival-free of dementia and persistent physical disability, and major cardiovascular events (cardiovascular death or non-fatal myocardial infarction or stroke). Secondary endpoints are all-cause death, dementia and other cognitive decline, persistent physical disability, fatal and non-fatal myocardial infarction, fatal and non-fatal stroke, heart failure, atrial fibrillation, fatal and non-fatal cancer, all-cause hospitalisation, need for permanent residential care and quality of life. Comparisons between assigned treatment arms will be on an intention-to-treat basis with each of the co-primary endpoints analysed separately in time-to-first-event analyses using Cox proportional hazards regression models.

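### Table 1's disability-free survival effect (14.5%) and power (83.1%) match a calculation that ignores the plan's own timing of those events; with that timing, about 13.7% and 78% at 1397 events

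*Protocol article*

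**What the plan says.** All the inputs are in the Sample size section of the protocol article. With adherence, "statins will reduce the rate of major cardiovascular events by 25% and the rate of disability-free survival by 18" per cent. Crossover then dilutes these effects. In the statin arm, year 1 is set as follows: "we assume 8% of participants randomised to statin will cease taking their study medication". For later years, "Thereafter we assume 3% of participants per annum in the statin group will cease taking study medication". In the placebo arm, 1% start open-label statin in year 1 and 3% a year after that. Nobody crosses back. Mean follow-up is 6.0 years.

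For DFS only, a healthy-participant rule is added. The stated age-specific rates apply from year 3, and in years 1 and 2 "the corresponding rates, respectively, will be zero and half of that of the third year of follow-up". No such rule is given for major cardiovascular events.

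The effect column of Table 1 is headed "Effect size (relative reduction in risk for statin group vs placebo in intention-to-treat analysis based on treatment adherence assumptions". Its entries are:

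- major cardiovascular events: 20.2%, power 80.0%, 619 events, 9631 participants;
- DFS: 14.5%, power 83.1%, 1397 events, 9631 participants.

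Testing is at a "two-sided significance level of 5% and adopting a closed testing procedure of the two co-primary endpoints".

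**The concern.** An intention-to-treat hazard ratio reflects adherence at the times when events happen. For an endpoint with a constant rate, an even average of crossover over follow-up is a fair approximation. Under the plan's rule DFS is not such an endpoint. Year 1 has the least crossover and contributes no events, and year 2 contributes half. Most DFS events fall in years 3 to 6, when more of the statin arm has stopped and more of the placebo arm has started. If the DFS row used the even average, its effect size and power do not follow from the assumptions printed beside it, and at a fixed 1397 events both are too favourable. DFS is a co-primary endpoint, so a null DFS result would be read against overstated power.

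**Working it through.** **Inputs** (Sample size section and Table 1): full-adherence reduction r = 0.25 (cardiovascular) and 0.18 (DFS); crossover of 8% then 3% a year (statin arm) and 1% then 3% a year (placebo arm); 6 years; two-sided 5%; 1:1 allocation; 619 and 1397 events. The article does not say how crossover was accumulated or averaged. The convention below (additive, mid-year) is inferred from its fit to Table 1.

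| Year | 1 | 2 | 3 | 4 | 5 | 6 |
|---|---|---|---|---|---|---|
| Off statin, statin arm (%) | 4.0 | 9.5 | 12.5 | 15.5 | 18.5 | 21.5 |
| On statin, placebo arm (%) | 0.5 | 2.5 | 5.5 | 8.5 | 11.5 | 14.5 |
| Even weight | 1 | 1 | 1 | 1 | 1 | 1 |
| DFS weight under the plan's rule | 0 | 0.5 | 1 | 1 | 1 | 1 |

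**Formulas.** HR = (1 − r × (1 − off)) / (1 − r × on). Power = Φ(|ln HR| × √events / 2 − 1.96). Events for a given power = 4 × (1.96 + z)² / (ln HR)².

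**Step 1: reproduce Table 1 with even weights.** Off = 81.5/6 = 13.58%; on = 43/6 = 7.17%.

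- Cardiovascular: HR = 0.7840/0.9821 = 0.7983, a reduction of 20.17%. Events for 80% power = 4 × (1.96 + 0.8416)² / 0.2253² = 618.4, so 619. Table 1 has 20.2%, 80.0% and 619.
- DFS: HR = 0.84445/0.98710 = 0.8555, a reduction of 14.45%. Power = Φ(0.1561 × 37.376/2 − 1.96) = Φ(0.957) = 83.07%. Table 1 has 14.5% and 83.1%.

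**Step 2: weight DFS by the plan's own timing.** Off = (0.5 × 9.5 + 12.5 + 15.5 + 18.5 + 21.5)/4.5 = 72.75/4.5 = 16.17%. On = (0.5 × 2.5 + 5.5 + 8.5 + 11.5 + 14.5)/4.5 = 41.25/4.5 = 9.17%. HR = 0.8491/0.9835 = 0.8633, a reduction of 13.67%. Power at 1397 events = Φ(0.1469 × 37.376/2 − 1.96) = Φ(0.786) = 78.4%. At this effect, 80% power needs 1455 events and 83.1% needs 1578.

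**Step 3: vary the convention, over the stated 6 years.**

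| Crossover taken at | Accumulation | Cardiovascular, even | DFS, even | DFS, with rule | DFS power at 1397, with rule |
|---|---|---|---|---|---|
| start of year | additive | 20.9% | 15.0% | 14.2% | 81.5% |
| start of year | multiplicative | 21.1% | 15.1% | 14.35% | 82.5% |
| mid-year | additive | 20.2% | 14.45% | 13.7% | 78.4% |
| mid-year | multiplicative | 20.4% | 14.6% | 13.9% | 79.8% |
| end of year | additive | 19.4% | 13.9% | 13.2% | 75.0% |
| end of year | multiplicative | 19.7% | 14.1% | 13.4% | 76.9% |

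With the rule, no row reaches 14.5% or 83.1%. Only mid-year additive reproduces all the effect and power figures of Table 1.

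Other horizons were also tried. Start-of-year crossover over five years gives 14.7% to 14.8% with the rule. However, it puts the cardiovascular effect at 21.6% to 21.8% and departs from the stated 6.0 years. Additive start-of-year over seven years (cardiovascular 20.2%) and additive end-of-year over five years (20.1%) both give 13.7% with the rule.

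**The case against.** The strongest objection is that the averaging method is inferred. The article does not say whether the 3% a year is additive or applies to those still on treatment, and the supplementary protocol and the appendix deriving the DFS rates are not shown. The heading of Table 1 ties the effect to adherence assumptions only and makes no claim to event-time weighting, so an unweighted average is compatible with that label. This stands to the extent that 13.7% and 78% are conditional figures. Mid-year multiplicative accumulation comes close to Table 1 and leaves power at about 80%. It does not rescue the printed row, because no six-year convention tried yields 14.5% or 83.1% once the plan's rule is applied.

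A second objection concerns weight. DFS is tested only if the cardiovascular endpoint succeeds, 9631 participants coincides with exactly 80.0% power in the unaffected cardiovascular row, and the effect moves by only about 0.8 percentage points. That limits the consequence but does not make the row correct.

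A reader might also infer that the 1397 events are wrong, or that DFS power is lower still because too few events will accrue. The documents do not support that. With fixed age bands, no depletion and the mean rate 0.56 × 18.3 + 0.27 × 33.9 + 0.12 × 65.7 + 0.05 × 115.4 = 33.06 per 1000 person-years, 9631 participants give about 1313 events with the rule (9631 × 0.03306 × 4.5 × 0.916) and about 1749 without it (9631 × 0.03306 × 6 × 0.916). The printed 1397 lies nearer the first, which suggests that the rule entered the event count but not the effect. That is an inference. The exact count depends on depletion and on whether participants move up age bands. The article ties the cardiovascular rates to age at randomisation but is silent for DFS.

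**Conclusion.** The DFS row of Table 1 is wrong as written: its effect and power do not follow from the assumptions stated with it. Under the inferred additive mid-year convention, the reduction is about 13.7% rather than 14.5%, and power at 1397 events is about 78% rather than 83.1%. The direction is the same for every six-year convention tried. The size rests on that convention, on the stated 6.0 years treated as common to all participants, and on the event count held at 1397. Staggered entry (assumed uniform from 2.5 to 9.5 years) would lower the figures further, to about 13.2% and 75%.

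It does not follow that the trial is too small. The cardiovascular row reproduces in full, and the sample size, the analysis and the testing order are untouched.

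**What to change.** Recompute the DFS row of Table 1 with crossover weighted by when DFS events are expected. On the additive mid-year convention this gives about 13.7%, with power about 78% at 1397 events. State the crossover convention (additive or multiplicative, and the point in the year at which it is taken) so that both rows can be checked. As a clarification only, say whether the DFS rates apply by age at randomisation or by attained age.

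The cost is one recalculated table row and a sentence or two of text. The stated DFS power becomes less favourable. Nothing in conduct, sample size or analysis needs to change.

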### Inclusion and exclusion criteria

Individuals are deemed eligible if they; (1) are aged ≥70 years; (2) live independently in the community; (3) are willing and able to provide informed consent and accept the study requirements and (4) do not have a history of clinical CVD events, diabetes or dementia. Exclusion criteria are a Modified Mini-Mental State Examination (3MS) score <78 on screening, moderate or severe chronic kidney disease, moderate or severe liver disease or serious intercurrent illness likely to cause death within the next 5 years; total cholesterol >7.5 mmol/L; current participation in another interventional clinical trial; and an absolute contraindication to statin therapy, current use of statin therapy or other lipid-lowering therapy for primary prevention and unwilling to stop therapy or current long-term or permanent use of potent cytochrome P450 3A4 inhibitors.

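### The sample size assumptions leave no room for any death in year 1 under disability-free survival, yet count cardiovascular deaths at the full rate from randomisation under major cardiovascular events

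*Protocol article*

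**What the plan says.** All of this stands in the Protocol article, mostly under Sample size.

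- **DFS.** Placebo rates run from 18.3 to 115.4 per 1000 person-years by age band. A healthy participant effect is then allowed for: "in the first and second year of follow-up the corresponding rates, respectively, will be zero and half of that of the third year of follow-up".
- **Major cardiovascular events.** The next assumption reads "Major cardiovascular event rates in the placebo group, according to age at randomisation, of 9.5 per 1000 person-years" for ages 70-74, rising to 24.5 at 85 and over. No early allowance is stated, and no reason for the difference.
- **Loss to follow-up.** 2% a year, said to include deaths, with no exception for year 1.
- **Shared component.** Under Primary objectives, DFS counts death from any cause and major cardiovascular events counts cardiovascular death.
- **Entry criteria.** Prior clinical cardiovascular events, diabetes, dementia and "serious intercurrent illness likely to cause death within the next 5 years" are all excluded.
- **Testing order.** Under Statistical analysis, major cardiovascular events is tested first. If it is not significant, no p value is given for DFS.
- **Table 1.** Major cardiovascular events: 20.2% effect, 80.0% power, 619 events. DFS: 14.5%, 83.1%, 1397 events. Both use 9631 participants.

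**The concern.** The same people are followed for both endpoints, and a cardiovascular death is an event for both. If no DFS event occurs in year 1, no cardiovascular death occurs in year 1. A cardiovascular rate that is flat from randomisation has such deaths in that year, unless every early event is non-fatal, which the article does not say. Both statements are listed as key assumptions of one power calculation.

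Major cardiovascular events is the gatekeeper and is planned at exactly 80.0% power, so it has no margin to absorb a shortfall. Whichever assumption gives way, a figure in Table 1 moves.

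**Working it through.** **Inputs from the article.** N = 9631, 1:1 allocation, two-sided 5%, 6.0 years average follow-up, age mix 56/27/12/5%, and a 25% reduction with full adherence. In the statin arm, "we assume 8% of participants randomised to statin will cease taking their study medication" in year 1, then 3% a year; in the placebo arm 1% start a statin in year 1, then 3% a year. Crossover is taken as linear within each year.

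**1. Reproduce Table 1 for major cardiovascular events, with flat rates.**
- Age-weighted placebo rate: 0.56×9.5 + 0.27×11.5 + 0.12×18.5 + 0.05×24.5 = 11.87 per 1000.
- Mean proportion on statin over 6 years: 0.864 (statin arm) and 0.072 (placebo arm). HR = (1 − 0.25×0.864)/(1 − 0.25×0.072) = 0.798, a 20.2% reduction (stated 20.2%).
- Events: 9631 × 6.0 × 0.01187 × (1 + 0.798)/2 = 617 (stated 619).
- Power: Φ(−ln 0.798 × √617/2 − 1.96) = 80.0% (stated 80.0%).

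The DFS allowance leaves 0 + 0.5 + 4 = 4.5 full-rate years. Applied to this endpoint it would give about 462 events at HR 0.798. Variants that remove people after an event, add 2% annual loss or let participants age into higher bands give 411-552 with the allowance. None comes near 619, so the allowance was not used here.

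**2. Confirm that it was used for DFS.** The age-weighted rate is 33.06 per 1000. With 4.5 full-rate years: 9631 × 4.5 × 0.03306 × (1 + 0.855)/2 ≈ 1329 events. With 6 years: about 1772. The stated 1397 lies close to the first.

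**3. Size of the conflict.** Flat rates give 617/6 ≈ 103 major cardiovascular events in year 1. Let *f* be the share that is cardiovascular death. The article does not give it, so 0.10-0.40 is assumed. Year 1 then holds 103 × *f* ≈ 10-41 cardiovascular deaths, against none under DFS.

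**4. If the DFS allowance is right for deaths.** Events = 103 × (6 − 1.5*f*). With reweighting, the years carry weights 1 − *f*, 1 − *f*/2, 1, 1, 1, 1 in both arms' average hazards.

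| *f* | Events | Power at HR 0.798 | Reweighted HR | Power |
|---|---|---|---|---|
| 0.10 | 601 | 79.0% | 0.799 | 78.5% |
| 0.20 | 586 | 78.0% | 0.800 | 77.1% |
| 0.30 | 570 | 76.9% | 0.801 | 75.6% |
| 0.40 | 555 | 75.7% | 0.802 | 74.0% |

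The reweighted rows have about one more event at most. Strictly, only year 1 is contradictory. Half the DFS rate in year 2 is 33.06/2 = 16.5 per 1000, which leaves room for 11.87 × *f* = 1.2-4.7 cardiovascular deaths per 1000. Removing year-1 deaths alone gives 617 − 10 to 617 − 41, about 606-576 events, and power of about 79-77% at HR 0.798.

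**5. If the cardiovascular rates are right.** The deaths missing from DFS number up to 1.5 × 103 × *f* ≈ 15-62, or 1.1-4.4% of 1397. Table 1 for major cardiovascular events is then unchanged.

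**The case against.** The strongest reply is that the cardiovascular rates have a different basis. They are tied to age at randomisation, and under Statistical considerations the event rates originally came from another trial's population. If they are averages over follow-up in a selected cohort, they already contain any entry effect, and a further allowance would count it twice. That may be so. The article does not say it, and its pointer to appendix 4 is attached to the DFS rates only. Even on that reading the zero DFS year still conflicts with the cardiovascular deaths assumed.

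The second reply is that an early gap suits DFS better. Persistent disability needs loss at two visits 6 months apart, and entry screening removes people close to dementia, dependence or death. Infarction and stroke have no confirmation delay. This stands, and it is why one allowance need not apply to both endpoints in full.

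Three stronger readings are therefore tempting but unsupported:
- **That the whole cardiovascular endpoint should carry the allowance.** This gives about 465 events, HR 0.809 and 63% power. It needs no infarction or stroke in year 1, which nothing in the article suggests. It is an extreme bound, not an expected effect.
- **That the two sets of rates are wholly incompatible.** Non-fatal infarction and stroke are not DFS events, so the clash does not reach them.
- **That the trial expects nobody to die in year 1.** The 2% annual loss includes deaths, so the zero is better read as a simplification in the DFS accrual. It then sits badly with that loss assumption too.

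Lastly, the simple accrual model gives 1329 DFS events against 1397, 5% low, so the results here are approximate.

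**Conclusion.** The inconsistency is real but limited. Under DFS no one can die in year 1; under major cardiovascular events cardiovascular deaths accrue at the full rate from randomisation, and the flat accrual is confirmed by Table 1's own figures. The documents do not show which assumption is wrong. If the cardiovascular side gives way, the gatekeeper loses about 1 to 6 points of power from 80.0%, depending on the assumed 10-40% share of cardiovascular death and on whether crossover is reweighted. If the DFS side gives way, its planned events are a few per cent too low and the gatekeeper's figures stand. Neither outcome undermines the design. The point merits correction because the gatekeeper has no spare power and the assumptions are easily reconciled.

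**What to change.** - Use one early-death assumption for both endpoints. Either allow DFS a year-1 rate compatible with the cardiovascular deaths assumed, or reduce the cardiovascular-death part of the other endpoint in the same years. The allowance for dementia and disability can stay separate, with its reason given.
- State whether the 9.5-24.5 per 1000 rates are follow-up averages that already include the entry effect, and state the assumed share of cardiovascular death.
- Check the year 1 and year 2 assumptions against blinded pooled rates from participants already enrolled.
- Restate events, effect and power in Table 1 for whichever endpoint changes.

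The cost is a recalculation and a short clarification. No extra participants or procedures are needed, but the stated power may become slightly less favourable.

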### Statistical analysis

Baseline characteristics of the two treatment groups will be tabulated and imbalance defined as a 0.25 SD difference in means (quantitative characteristics) or an OR of 1.5 (binary characteristics). Given the large sample size, randomisation is anticipated to adequately balance baseline characteristics of participants in the two treatment groups. Hence unadjusted analyses will be considered primary. All primary comparisons between treatment arms will be on an intention-to-treat basis, that is, according to the group to which participants were randomised and without reference to their actual compliance with assigned treatment. Each of the co-primary endpoints will be analysed separately in time-to-event analyses. Event rates (time to first event within each endpoint definition) will be compared between groups using an HR and 95% CI from a Cox proportional hazards regression model fitted to the endpoint, with censoring for individuals not experiencing an endpoint event at their most recent study visit, and a single covariate being an indicator of the group to which the individual was randomised, statin or placebo. The proportional hazards assumption will be tested for each model. Loss to follow-up will be considered a censoring event. This equates to an assumption that data is missing at random given the participant’s treatment group and the timing of their loss to follow-up. The adequacy of this assumption will be checked in sensitivity analyses that will include both imputation approaches and adjustment for baseline covariates predictive of propensity for dropout.

A closed testing procedure will be used to allow for the multiple testing arising from two co-primary endpoints. This approach is based on the expectation that cardiovascular benefit will be the main contributor to improved disability-free survival and that a substantial effect of statins on the latter is unlikely in the absence of an effect on the former. First, major cardiovascular events will be tested at alpha=0.05 and, if the major cardiovascular events p value is <0.05 then second, disability-free survival will be tested at alpha=0.05. If the major cardiovascular events p value is not <0.05 than a p value for disability-free survival will not be presented.

Secondary analyses of the co-primary endpoints will be performed using extended Cox proportional hazards regression models based on time(s) to any event within the endpoint definition (for relevant endpoints that can occur more than once). No statistical adjustment will be made for the multiple secondary endpoints and no p values will be presented for the statin versus placebo comparison for these endpoints. The reporting of all secondary endpoint analyses will make clear whether either of the co-primary endpoints were statistically significant.

Subgroup analyses will be undertaken by sex (female, male), age (70–74, ≥75 years), systolic and diastolic blood pressure levels (terciles), body mass index (<25, 25–29.9, 30+ kg/m^2^), smoking status (never, past and current), 3MS score (above, below median), eGFR (<60, ≥60 mL/min per 1.73 m^2^) and LDL-C and HDL-C levels (terciles).

The impacts of COVID-19 will be investigated in sensitivity analyses that include examination of participant event rates by whether their randomisation occurred pre-pandemic, peri-pandemic or post-pandemic, and consider COVID-19 vaccination status (which will be an intercurrent event for those randomised pre-pandemic and a baseline covariate for those randomised post-pandemic), following emerging guidance on analytical approaches and estimand definitions.^52^

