### Study objectives and hypotheses

#### Primary objectives

To determine in people aged ≥70 years the effect of statin therapy (40 mg atorvastatin) versus placebo, on two co-primary clinical endpoints:

Disability-free survival defined as survival free of dementia and persistent physical disability (a composite of all cause death or development of dementia or persistent physical disability); andMajor cardiovascular events (a composite of cardiovascular death, non-fatal MI or non-fatal stroke).

We hypothesise that treatment with a statin (atorvastatin 40 mg) will: (1) prolong overall disability-free survival, and (2) reduce the incidence of major cardiovascular events among a primary prevention population aged ≥70 years.

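### Table 1's 83.1% power for disability-free survival is stand-alone power; under the stated testing sequence it cannot exceed 80.0% and is about 66–73%

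*Protocol article*

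**What the plan says.** The Sample size section of the protocol article introduces Table 1 as giving requirements "with a two-sided significance level of 5% and adopting a closed testing procedure of the two co-primary endpoints". Table 1 then has one row per co-primary endpoint, both at 9631 participants:

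- MACE: 20.2% reduction, 80.0% power, 619 events.
- DFS: 14.5% reduction, 83.1% power, 1397 events.

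Neither power is labelled as marginal, conditional or joint.

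The Statistical analysis section defines the procedure. MACE is tested at 0.05 and, "if the major cardiovascular events p value is <0.05 then second, disability-free survival will be tested at alpha=0.05". In the other case, "If the major cardiovascular events p value is not <0.05 than a p value for disability-free survival will not be presented". The reason given for the order is that "cardiovascular benefit will be the main contributor to improved disability-free survival".

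**The concern.** The article states three things: the testing sequence, a table said to adopt it, and a DFS power above the MACE power. If the 83.1% is read as the chance of declaring DFS under the sequence, they cannot all hold. An endpoint that is tested only after another has succeeded cannot be declared more often than that other endpoint.

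DFS is a co-primary endpoint, and the Discussion presents it as the way the trial goes beyond traditional statin outcomes. The design was finalised in July 2021 with the target reduced from 18 000, so Table 1 is the justification that funders and readers will rely on. Someone who takes 83.1% as the chance of a confirmatory DFS result, should the planning assumptions hold, would be misled.

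**Working it through.** **Inputs.** From Table 1: 619 events and hazard ratio (HR) 1 − 0.202 = 0.798 for MACE; 1397 events and HR 1 − 0.145 = 0.855 for DFS; stated powers 0.800 and 0.831. Two-sided 5% is from Sample size, 1:1 allocation from the Abstract, and the sequence from Statistical analysis. The event counts and intention-to-treat effects are taken as given.

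**Step 1: reproduce the stated powers, one endpoint at a time.** With d events and 1:1 allocation, Schoenfeld's formula is power = Φ(½ √d · |ln HR| − 1.960).

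- DFS: ½ × √1397 × |ln 0.855| = 18.69 × 0.1567 = 2.928. Φ(2.928 − 1.960) = 83.3%. Rounding of the HR gives 83.1% to 83.6%, and Freedman's formula gives 83.2%.
- MACE: ½ × √619 × |ln 0.798| = 12.44 × 0.2257 = 2.807. Φ(2.807 − 1.960) = 80.2%. Freedman's formula gives 79.8%.

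Both entries in Table 1 are thus reproduced as stand-alone powers at the full 5%. The sequence has not been applied to the DFS entry.

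**Step 2: bound without any assumption.** Under the sequence,

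P(DFS declared) = P(MACE significant and DFS significant) ≤ P(MACE significant) = 80.0%.

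So 83.1% exceeds the most that the procedure can deliver by at least 3.1 points, whatever the correlation.

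**Step 3: power under the sequence.** Treat the two test statistics as bivariate normal with correlation ρ and the stated marginal powers. Then P(both significant) = Φ₂(0.842, 0.958; ρ), where 0.842 and 0.958 are the normal quantiles of 0.800 and 0.831.

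The article does not give ρ. A usual approximation is ρ ≈ (participants with both events) / √(619 × 1397). The upper end takes every MACE participant as also having a DFS event: 619 / √(619 × 1397) = 0.67. This is generous. DFS is "a composite of all cause death or development of dementia or persistent physical disability" and MACE is "a composite of cardiovascular death, non-fatal MI or non-fatal stroke", so only cardiovascular death counts automatically towards both.

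| ρ | Basis | P(DFS declared) | Shortfall from 83.1% |
|---|---|---|---|
| 0 | uncorrelated (0.800 × 0.831) | 66.5% | 16.6 points |
| 0.21 | 200 shared participants | 68.1% | 15.0 points |
| 0.43 | 400 shared participants | 70.1% | 13.0 points |
| 0.67 | all 619 shared | 72.7% | 10.4 points |
| 1 | mathematical limit | 80.0% | 3.1 points |

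**Step 4: could 83.1% be the power of the DFS test given that MACE has succeeded?** Dividing the joint power by 0.800 gives 83.1% at ρ = 0, 85.0% at ρ = 0.2, 86.1% at ρ = 0.3 and 90.9% at ρ = 0.67. The figure fits that reading only at zero correlation.

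**The case against.** The best defence is that nothing in Table 1 is miscalculated. Each row pairs one effect, one event count and one power, and reporting power endpoint by endpoint is common under a fixed sequence. The mention of closed testing may be there only to explain why each endpoint is powered at the full 5% and not at a split level. The sequence itself is stated openly. All of this stands, and it probably explains how 83.1% arose. It does not make the figure the power under the procedure to which the section ties the table, and nothing in the table warns the reader.

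Three stronger readings are tempting, and the article does not support them.

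- *The 83.1% is an arithmetic error.* It is not: it is reproduced as stand-alone power. What is missing is the label and the second figure.
- *The sequence costs DFS a one-in-three chance of a confirmatory result.* The chance of no DFS claim is 27% to 34%, and only the uncorrelated end is near one in three. Shared cardiovascular deaths and the article's own rationale both point to positive correlation. Of that chance, 16.9 points are the ordinary type II error of a test with 83.1% power. The sequence adds 10 to 17 points. When the first test fails, the article withholds the DFS p value; it does not say that the estimate is withheld.
- *The testing procedure should be replaced.* The fixed sequence holds the familywise error rate at 5%, and the article gives a reason for the order. A Hochberg procedure would raise DFS power to about 80–81%, but would lower MACE power to about 78%, below the 80.0% in Table 1. That is a design trade-off and does not correct an error.

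**Conclusion.** The point holds as a matter of how power is stated. The 83.1% for DFS is the power of that test considered alone. Under the stated sequence the power to declare DFS is at most 80.0%, which follows from the article's own figures with no further assumption. It is about 66–73% for correlations from 0 to 0.67. That range rests on Table 1's event counts and effects, on a bivariate normal approximation, and on an assumed correlation whose upper end is generous.

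The 80.0% for MACE, both event targets, the 9631 participants, the type I error control and the planned analysis are unaffected.

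**What to change.** In Table 1, label 83.1% as stand-alone (marginal) power. Add the power to declare DFS under the stated sequence, about 66–73%, with the correlation range of 0 to 0.67 shown beside it. If the investigators can estimate how many participants will have both a MACE and a DFS event, for example from blinded pooled data, they can narrow the range.

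The cost is a label and a footnote. There is no change to the sample size, the event targets, the order of testing or the analysis.
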